#### Predictors of Medication Adherence

To determine the factors related to medication adherence, we will examine sociodemographic, clinical, and psychosocial variables. The variables that show at least a moderate correlation and have a significant relationship to medication adherence (*P*<0.10) will be included in a multiple regression analysis in which medication adherence is the dependent variable. The multiple regression analysis will provide the optimum combination of these variables to explain the total percent of variance in medication adherence, and indicate the unique contribution of each variable to the regression model.

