#### Other Variables and Instruments

We will examine other variables (health-related quality of life, social support, self-efficacy, depression, anxiety, and post-traumatic stress disorder) and their relationship to medication adherence. Patients will complete the instruments at baseline, 1, 6, and 12 months (Table 3).

**Table 3 table3:** Instruments used to assess additional variables.

Measure	Description	Months					
		0	1	3	6	9	12
Health-related quality of life	The 12-Item Short Form Health Survey (SF-12) is the shorter version of SF-36, which measures functional health and well-being (relative validity median 0.67 and 0.97 for the physical and mental components, respectively) [44].	x	x		x		x
Social support	The 20-item Medical Outcomes Study Social Support Survey Instrument uses multi-trait scaling analyses of 4 functional support scales and provides an overall functional social support index (Cronbach alpha=0.91) [45].	x	x		x		x
Medication self-efficacy	The 13-item Self-Efficacy for Appropriate Medication Use Scale measures how confident individuals are in taking their medications correctly in certain situations (Cronbach alpha=0.89) [46].	x	x		x		x
Depression	The 9-item Patient Health Questionnaire is used to diagnose and measure the severity of depression as well as monitor response to treatment (Cronbach alpha=0.89) [47].	x	x		x		x
Anxiety	The 7-item Generalized Anxiety Disorder Assessment is used to screen and measure severity of generalized anxiety disorder (Cronbach alpha=0.92) [48].	x	x		x		x
Post-traumatic stress disorder	The 17-item Post-Traumatic Stress Disorder Checklist: Civilian is a popular self-report rating scale for post-traumatic stress disorder. The civilian version will be used instead of the military version because the majority of participants will not have been on recent active duty, >35% of Veterans with post-traumatic stress disorder had a nonmilitary trauma, and non-Veteran women will be included (29%; Cronbach alpha=0.87) [49].	x	x		x		x

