#### Primary Statistical Analysis

Our primary analysis will use a mixed-effects linear model. The predictors will be a categorical predictor of group (with control as reference), time, and the group-by-time interactions, as well as the recruitment site (SFVAMC vs JMMC), as randomization is stratified by site. The parameters in the group-by-time interaction are the primary parameters of interest, describing whether adherence changes differentially over baseline in each of the treatment groups compared to the control group. We will also investigate whether other models for change over time are more appropriate, including arbitrary means or nonlinear time functions through comparison of Akaike information criterion/Bayesian information criterion. Secondary analyses will adjust for select covariates that are strongly associated with adherence.

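### Screening predictors one at a time on adherence, then fitting the survivors on the same data, cannot give the best joint set and makes the reported percent of variance optimistic

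*Protocol article*

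**What the plan says.** The rule is in the protocol article under Predictors of Medication Adherence. The candidates are broad: "we will examine sociodemographic, clinical, and psychosocial variables". They are filtered on their individual relation to the outcome: "The variables that show at least a moderate correlation and have a significant relationship to medication adherence", with P<0.10 as the significance limit. Those that pass "will be included in a multiple regression analysis in which medication adherence is the dependent variable". The article then says what the fitted model delivers: "will provide the optimum combination of these variables to explain the total percent of variance in medication adherence", together with the unique contribution of each variable.

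Moderate is given no number. The section mentions no shrinkage, validation or allowance for the selection step.

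The primary mixed-effects model is specified separately, under Primary Statistical Analysis, and does not use this screen.

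**The concern.** The same adherence values choose the variables and then measure how well they do. Two problems follow.

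- **The set.** A variable's value in a joint model depends on the other variables in it. Filtering on single-variable correlations can drop a variable that matters jointly, so the result has no claim to be the best combination.
- **The fit.** Variables pass partly because chance pushed their sample correlation up. R² computed afterwards on the same participants keeps that luck, and the coefficients of weak survivors carry it too.

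At stake is the credibility of one planned output: which characteristics relate to adherence, how strongly, and how much variance they explain. The undefined cut also leaves room to settle the model after the correlations have been seen.

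**Working it through.** **Sample size.** Sample Size Estimation gives 225 enrolled and 15% attrition. Per arm, 75 × 0.85 = 63.75, about 64, and 3 × 64 = 192 as stated. The stated 86% power also reproduces (86.1%: two-sided Dunnett at 0.05, half-SD effect in both active arms, at least one detected). It concerns the group comparison; no figure is given for the predictor regression.

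**Which half of the rule binds.** For a two-sided P of 0.10 with 190 df, t = 1.653. The smallest significant correlation is r = t/√(df + t²) = 1.653/√(190 + 2.73) = 0.119. Any usual reading of moderate is stricter, so the unnumbered cut decides entry.

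**Chance of being kept.** Use Fisher's z with standard error 1/√189.
- Cut 0.3, true r=0.20: (0.3095 − 0.2027) × 13.75 = 1.47, so about 7% are kept.
- Cut 0.3, true r=0.30: difference 0, so about 50%.
- Cut 0.2, true r=0.20: difference 0, so about 50%.
- P<0.10 alone, true r=0.30: (0.1198 − 0.3095) × 13.75 = −2.61, so more than 99%.

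**Simulation of the whole rule.** Assumptions that the article does not fix: normal data, independent candidates, either 20 candidates with 5 real or 15 with 4 real, and the meaning of moderate. R² is averaged over runs in which at least one variable survives.

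| Cut on absolute r | True r | Candidates (real) | Real predictor kept | Mean coefficient if kept | Reported R² | Out-of-sample R² |
|---|---|---|---|---|---|---|
| 0.3 | 0.20 | 20 (5) | 7% | 0.325 | 0.12 | 0.02 to 0.03 |
| 0.2 | 0.20 | 20 (5) | 51% | about 0.25 | 0.17 | 0.09 |
| 0.3 | 0.30 | 15 (4) | 51% | 0.335 | 0.25 | 0.18 |

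In the first row no variable survives in 68% of runs. In the third, all real predictors together explain 4 × 0.30² = 0.36. Reported R² is therefore too high for the retained set and still below what the candidates could explain.

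**Adjusted R² after the screen is not a cure.** With 15 candidates intercorrelated at 0.3, marginal r=0.30 and cut 0.3, R² is 0.18 and adjusted R² 0.17, while the retained set truly explains 0.13.

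**No real predictors, P<0.10 alone, 15 candidates.** Expected false entries are 15 × 0.10 = 1.5. The chance of at least one is 1 − 0.9^15 = 79%.

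**Why marginal screening misses a joint predictor.** Take two predictors correlated 0.6 with standardised coefficients 0.5 and −0.3. The second has marginal correlation −0.3 + 0.6 × 0.5 = 0. It passes P<0.10 in about 10% of runs and a 0.3 cut in none, although the joint model detects it with 95% power.

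**Comparison: all 15 candidates, no screen.** Coefficients average 0.30 and 0.20 for true values of 0.30 and 0.20, interval coverage is about 95%, and adjusted R² is 0.359 (true 0.36) and 0.159 (true 0.16).

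**The case against.** The strongest reply is that the size of the harm comes from the assumptions. The article fixes neither the cut, the number of candidates nor the true correlations. A plan that seeks at least moderate correlates may reasonably pass over r=0.20. With P<0.10 alone and true r of 0.30 or more, fewer than 1% of real predictors are lost and coefficient bias is small. Even with a 0.3 cut, survivors with true r=0.30 average 0.335 with 96% coverage. All this stands, so a reader who infers that the rule would miss most real predictors whatever the data goes too far. Nor is every survivor overstated: with intercorrelated candidates and P<0.10 alone, the mean coefficient was slightly low (0.149 against 0.158).

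Four further inferences are tempting and not supported.
- **The adjusted treatment analysis.** Primary Statistical Analysis says "Secondary analyses will adjust for select covariates that are strongly associated with adherence". It gives no threshold and does not say that the association is judged in the trial's own data, so the same screen cannot be read into it.
- **The later multi-site study.** The article ties improvements for that study to the qualitative process evaluation, not to this regression.
- **Timing and randomised group.** "Patients will complete the instruments at baseline, 1, 6, and 12 months", and the predictor section names neither the visit used nor randomised group. In a condensed article that is silence, not error.
- **Confidence intervals.** The section promises none, so poor coverage is a property of the method and not a false statement in the plan.

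What does not yield is the core: the screening rule is stated, and so is a reading of its result that the rule cannot support.

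**Conclusion.** The point holds as a fault in a stated method for a secondary, explanatory analysis. Two parts do not depend on the scenarios: marginal screening does not identify the best joint set, and at n=192 the undefined moderate cut is the working filter. The sizes do depend on them. With cuts of 0.2 to 0.3 and true correlations of 0.20 to 0.30, reported R² exceeds out-of-sample R² by 0.07 to about 0.10, and between about 7% and half of real predictors are kept in the scenarios tabulated. Inflation of coefficients is marked for weak predictors under a strict cut and slight for stronger ones. The randomised comparison, the primary model and the sample size are untouched. The change is worth making because it is cheap, but the trial's main conclusion does not hang on it.

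**What to change.** Remove the correlation and P<0.10 screen. Fit one model with a candidate list fixed before the outcome data are examined: baseline values of the Table 3 scales, a short set of sociodemographic and clinical variables, site and randomised group. Report every partial coefficient, and an adjusted or bootstrap-corrected R². Drop the claim to the optimum combination. If the list must be shortened, use penalised regression with bootstrap validation that repeats the selection in each resample.

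The cost is wording only, with no new data or visits. At n=192, 15 candidates leave 192/15 = 12.8 participants each and 20 leave 9.6. The price is wider intervals, which may not be slight. If the six psychosocial measures were correlated 0.5 to 0.7 with one another (an assumption), the variance inflation factor (1 + 4ρ)/[(1 − ρ)(1 + 5ρ)] would be 3/1.75 = 1.7 to 3.8/1.35 = 2.8. Their intervals would then be about 31% to 68% wider than with uncorrelated predictors. That argues for a short list, not for a screen.

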#### Process Evaluation

The in-depth individual interviews for process evaluation will be transcribed, coded, and analyzed in the same manner as in Aims 1 and 2. We will explore reasons for attrition over the 12-month period. We will complete field notes after the conclusion of each interview, and all interviews will be transcribed verbatim. Thematic analysis will include reading the completed field notes and interview transcripts. The key outcomes will be related to patient satisfaction and process evaluation, particularly focusing on how views vary across groups.

## Results

We began enrollment for the Mobile4Meds focus groups in January 2017. The focus group data will inform the development of the RCT, which is scheduled to begin in early 2018. We anticipate this four-year research study will be completed in late 2020.

We believe that participants will provide valuable contributions on the content and frequency of text messaging in Aim 1. We expect that focus groups that are stratified by low/high mobile phone use and sex will have differing opinions on frequency of text messaging delivery; however, we also predict that the perceived usefulness of text messaging content will be similar across groups. Based on participants’ responses, we will refine our text messaging content and frequency in preparation for Aim 3.

By conducting Aim 2, we will complete a content analysis of the top 10 commercially available mobile apps that will provide an evidence-based guide for health researchers and clinicians. We expect that using the top 2-4 selected mobile apps over 2-4 weeks on participants’ personal smartphones will provide clear insight into which mobile app should be used for the RCT.

This study is powered to prove the efficacy of using different mobile strategies to promote adherence to antiplatelet medications. By conducting Aim 3, we will compare two mHealth strategies (with a website-control condition) among Veterans using multiple methods to assess adherence. We will also examine the relationship between medication adherence and important variables (ie, health-related quality of life, social support, self-efficacy, depression, anxiety, and post-traumatic stress disorder). The study duration of 12 months, which is the recommended duration of antiplatelet use for most MI/PCI patients, will provide valuable information about patterns of medication adherence.

## Discussion

Evaluating the clinical application of mHealth strategies through rigorous scientific design and methodology is an important step in establishing whether there is potential for long-term benefit among Veterans who live with chronic disease [50]. The best way to ensure strict medication adherence in patients has continued to elude health care providers. Worldwide development and adoption of mobile technology has successfully spurred dramatic growth of mHealth as a platform to deliver intervention strategies for various health conditions in the past several years [51].

Researchers suggest that patient knowledge, self-monitoring, counseling, accountability, and a personalized program can contribute to improvement in medication adherence [52]. Experts and multiple stakeholders in medication adherence agree that a patient-centered approach is necessary, and increasing patient knowledge is critically important [25]. Technological solutions have been suggested to alleviate medication nonadherence, such as mHealth technology, electronic monitors, pill-monitoring technology, online resources, and social media [52]. The best manner to engage with Veterans via text messaging and mobile apps has yet to be determined among those of different ages, sexes, chronic diseases, mobile phone usage patterns, and ethnic populations. There are many opportunities to explore these unanswered questions in future studies.

### Limitations

There are potential limitations associated with this study. In Aims 1 and 2, if we do not reach saturation of ideas or if we find distinct differences between groups, we may add a mixed-group to tease out differences. We may also add an additional focus group of mixed and unstratified participants to identify differences. Alternatively, we will conduct structured one-on-one interviews to acquire richer information as a supplement to the focus groups.

In Aim 3, a limitation may be attrition due to Veteran disinterest in receiving text messages or using a mobile app for 12 months. We will address the potential barrier of disinterest during the two focus groups, as planned in Aims 1 and 2, and ask Veterans how to best engage with them after ACS/PCI over 12 months. Multiple strategies will be used to maximize participant retention and decrease missing data, since the intervention is intended to last 12 months. The dropout or missing data rates for the three groups will be examined to see that they are significantly different. Sensitivity analyses will include a complete-case analysis.

Another potential limitation may be cross-over effects for the text messaging and website (control) groups if they use a mobile app concurrently during the RCT. We will request that patients not use any other electronic medication reminders, including on their mobile phones (eg, alarm, app). At the conclusion of the study, we will ask participants in the text messaging and control groups if they used any other electronic reminders. If they have, we will conduct sensitivity analyses as described.

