#### Baseline Data Collection

After written consent is obtained, we will collect clinical data by reviewing electronic medical records. Participants will complete the following baseline questionnaires: (1) sociodemographic information and medical history, (2) mobile phone use, and (3) Mini-Cog Test [39]. All instruments and frequency of administration are described in Table 2.

**Table 2 table2:** Measurement of medication adherence with intervals.

Measure	Description	Rationale	Months					
			0	1	3	6	9	12
Key Primary Endpoint								
Medication Event Monitoring System (MEMS) [40]	Electronic pill caps time stamp when the bottle is opened, correlating with intake of medication. Primary outcome is percentage (0-100%) of prescribed doses taken	Most objective, noninvasive method and considered the “gold standard”		x		x		x
Secondary Patient-Reported Endpoints								
MEMS [40]	Percentages (0-100%) of (1) days correct doses are taken, and (2) doses taken on schedule	Most objective, noninvasive method and considered the “gold standard”		x		x		x
Morisky Scale [41,42]	Eight-item Morisky Medication Adherence Scale (MMAS-8) self-reported questionnaire on adherence behavior for a range of scores 0-8, with higher scores indicating poor adherence (Cronbach alpha=0.83).	Most popular scale and well-validated instrument with high reliability	x	x		x		x
7-Day Recall	One item asking how many days in the past week patient remembered to take medications. Final outcome is a percentage (0-100%).	Most commonly used method in the clinical setting	x	x		x		x
Secondary Objective Endpoints								
Veterans Affairs Corporate Data Warehouse (Veterans)	Veterans Affairs software program that provides detailed information on inpatient and outpatient medications. Final outcome is a percentage (0-100%) of days covered during 90-day period.	Assesses adherence via 90-day refill patterns (does not require active participation)		x	x	x	x	x
Peoplechart Meds Incontext (non-Veterans)	Private software program that uses refill data directly from retail pharmacies and Personal Benefits Manager. Final outcome is a percentage (0-100%) of days covered during 90-day period.	Assesses adherence via monthly refill patterns (does not require active participation)		x	x	x	x	x

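### The one sensitivity analysis named for dropout, a complete-case analysis, cannot test the adherence-related attrition the protocol anticipates, and the reminder-use analysis points back to it although it does not address contamination

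*Protocol article*

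**What the plan says.** All the wording at issue is in the protocol article, Discussion, Limitations, unless stated otherwise.

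- **Expected attrition.** In Aim 3, "a limitation may be attrition due to Veteran disinterest in receiving text messages or using a mobile app for 12 months".
- **Stated responses.** Retention strategies; a comparison of dropout, "The dropout or missing data rates for the three groups will be examined to see that they are significantly different" (presumably meaning whether they differ); and "Sensitivity analyses will include a complete-case analysis".
- **Contamination.** The cross-over named is "cross-over effects for the text messaging and website (control) groups if they use a mobile app concurrently during the RCT". The request made of participants carries no arm restriction: "We will request that patients not use any other electronic medication reminders, including on their mobile phones (eg, alarm, app". At the end of the study, "we will ask participants in the text messaging and control groups if they used any other electronic reminders". The analysis is then given as "If they have, we will conduct sensitivity analyses as described".
- **Primary analysis.** Under Primary Statistical Analysis, a mixed-effects linear model with group, time, their interaction and site.
- **Data that do not depend on attendance.** Table 2 says of the Veterans' refill measure: "Assesses adherence via 90-day refill patterns (does not require active participation". The non-Veteran refill measure is described in the same way, and both are scheduled at 1, 3, 6, 9 and 12 months.

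**The concern.** Under the protocol only two of the three arms receive texts or an app, so dropout through loss of interest in them is tied to allocation. People who lose interest in adherence support plausibly take fewer doses. If they leave, those who remain in the intervention arms look more adherent than the arm as randomised.

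A useful sensitivity analysis would ask how far the result depends on the missing patients being like the observed ones. The complete-case analysis does not ask this. If its result agrees with the primary one, a reader may take that as confirmation when both are shifted in the same direction.

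For other reminders, the protocol names contamination as a threat, but its cross-reference leads only to a missing-data analysis. The information collected also leaves out one arm, and it may leave out everyone who has already left.

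**Working it through.** **1. The plan's own figures.** Sample Size Estimation: 225 × 0.85 = 191.25, given as 192, or 64 per arm. A two-sided 5% Dunnett test (level and sides assumed; two comparisons, 189 df, simulated critical value 2.23), with both active arms 0.5 SD above control, gives 86.2% power for at least one difference. The article states 86%, so the figure reproduces and is not in question.

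**2. Assumptions compared.** The mixed model uses partial records and remains valid if dropout depends on arm, site and adherence already observed. The complete-case analysis discards the partial records and is generally valid only if, given arm and site, dropout is unrelated to adherence. It therefore assumes more than the analysis it is meant to test, and neither allows dropout to depend on unobserved adherence.

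**3. Bias in completer means.** With dropout proportion p, completer mean C and dropout mean D, the mean of all randomised is (1 − p)C + pD, so completers overstate it by p(C − D). Assume 20% dropout in an intervention arm, 10% in control, and dropouts 30 points less adherent (range 15 to 45):

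- 0.20 × 30 − 0.10 × 30 = 3 points
- at 15: 3.0 − 1.5 = 1.5 points
- at 45: 9.0 − 4.5 = 4.5 points

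For scale, if the pilot's 15 to 17 point gain corresponds to d = 0.69, half an SD is 15/0.69/2 = 10.9 to 17/0.69/2 = 12.3 points. The article does not state that correspondence.

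**4. Complete-case against mixed model.** A simulation used a true effect of zero and visits at 1, 6 and 12 months. In the active arm, 85% of dropouts came from the lower half of month-12 adherence; control dropout was random. All inputs are assumed.

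| Dropout, active / control | Complete-case bias | Missing-at-random likelihood bias |
|---|---|---|
| 15% / 15% | +0.10 SD | +0.05 SD |
| 20% / 10% | +0.14 SD | +0.07 SD |
| 25% / 5% | +0.19 SD | +0.10 SD |

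The complete-case estimate errs in the same direction and about twice as far.

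**5. The dropout comparison.** For 20% versus 10% at 75 per arm, SE = √(0.20 × 0.80/75 + 0.10 × 0.90/75) = 0.058, and 0.10/0.058 = 1.73. Power at two-sided 5% is Φ(1.73 − 1.96) = 0.41. The first row of the table also shows that equal dropout rates do not rule out bias.

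**6. Contamination.** Suppose the true app-versus-website effect is 0.5 SD and 20% of website patients use an app and gain 0.5 SD. The comparison as randomised is 0.5 − 0.20 × 0.5 = 0.40 SD. Restricting to completers leaves this dilution unchanged if users and non-users drop out equally, so the complete-case result says nothing about it.

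**7. Who is asked.** On the plan's own attrition figure, two arms of 64 completers, or 128 of 225, would be present to answer. About 2 × (75 − 64) = 22 dropouts from those arms may be missed, and all 75 in the app arm are not asked.

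**The case against.** **The list is open.** The sentence says what the sensitivity analyses will include, in a journal article whose full analysis plan is not shown. A reader might infer that complete-case is the only one planned; the text does not support that. Nor is the absence of a tipping-point analysis a fault in itself. What remains is that the one method the article does fix is unsuited to the attrition described in the same paragraph.

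**Exclusion of reminder users is not stated.** A reader might infer that users will be removed in two arms and kept in the third, which would break the randomised comparison. The document never says so, and a complete-case analysis does not by definition remove them. The firm defect is that the cross-reference leaves the reminder-use analysis without a method suited to contamination.

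**The question does reach the named cross-over.** The protocol names app use in the text messaging and website arms, and those are the two arms asked. It would be wrong to say that it cannot detect this contamination. What it misses is alarms or a second app in the app arm, which the general request covers, and use by those who left early.

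**There are other safeguards.** The mixed model remains primary, and refill-based days covered is a planned secondary outcome that depends less on attendance. Both help, but neither tests how the primary estimate responds if dropouts are less adherent.

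**The size is assumed.** The article gives only 15% attrition overall; the arm-specific rates and the adherence gap are not in it. This stands.

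**Conclusion.** The point holds in limited form. The conclusion about dropout follows from the assumptions of the two analyses and does not depend on the illustrative numbers: a complete-case analysis cannot test departures from missing at random, and its agreement with the mixed model would not be reassuring if dropouts are less adherent. A non-significant difference in dropout rates adds little, at about 41% power under the assumed rates.

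The size is illustrative only. On the stated assumptions it is about 1.5 to 4.5 points in completer means, roughly a quarter of an 11 to 12 point target at the central value (3/12.3 to 3/10.9, or 24% to 28%), and about half as much under a missing-at-random model in the simulation. The documents do not show that such bias will occur.

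For other reminders, the analysis referred to does not address contamination, and use is recorded for only part of the trial population. This should be changed, but it does not undermine the design or the sample size.

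**What to change.** **(a) Dropout.** Replace the complete-case analysis with a sensitivity analysis of all randomised patients, or rank it below one. Use multiple imputation with earlier electronic-monitoring data and refill days covered as auxiliary variables; refill data can continue after monitoring stops, provided access to records continues. Add an arm-specific delta or tipping-point analysis that shows how much less adherent dropouts would have to be to change the conclusion. Report dropout by arm and do not rely on a significance test.

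**(b) Other reminders.** Ask about them in all three arms at the 1-, 6- and 12-month visits already planned. Keep every patient in the arm as randomised for the main comparison, and report reminder use by arm in place of the reference back to the complete-case analysis. A complier-type analysis is at most an optional supplement: with three arms and mixed reminder types, its assumptions are hard to defend.

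**Cost.** More analysis work and one extra question at existing visits; no new visits or procedures.
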